### Procedure

The Ethics Committee of Ulm University approved this study. We will invite individuals interested in participating in the study to a telephone-based interview. Here, they will receive detailed study information and give oral informed consent. A pre-screening will assess eligibility (t_1_, see Figs. 1 and 2). At an appointment at Ulm University, successfully pre-screened participants will be able to give written informed consent and will undergo further screening (t_2A_). For included participants, the procedure will consist of a 1.5-h pretest assessment composed of neuropsychological tests and questionnaires (t_2B_) followed by the face-to-face cognitive health counseling (t_2C_). Subsequently, non-blinded study staff will disclose the group allocation to the participants (t_2D_). Within 2 weeks after the baseline assessment, the 5-week intervention period will start. We will contact all participants three times via telephone for cognitive health counseling and the assessment of adverse events (AEs, t_3_ – t_5_). These telephone-based interviews will also serve to monitor the jigsaw puzzle experience and protocol adherence in the jigsaw puzzle group. Within 2 weeks after the intervention period, we will assess the same outcomes as in the pretest assessments in the 1.5-h posttest assessment at Ulm University (t_6_). Psychologists who are blind to group allocation will conduct the pretest and posttest assessments.

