#### Predictive variables of cognitive decline and dementia

The investigators will obtain the predictive socio-demographic variables age, gender, years of education, and main profession, using interview-based questionnaires. Three questions on the subjective degree of jigsaw puzzle experience on a 5-point rating scale (answers range from “very high” to “not at all”), the number of jigsaw puzzle hours, and the number of connected jigsaw puzzle pieces within participants’ lifetime will assess lifetime jigsaw puzzle experience. The assessment of risk factors for cognitive decline and dementia with self-rating questionnaires will include items on high blood pressure, hypercholesterolemia, diabetes mellitus, smoking, alcohol misuse, and obesity. The newly developed Challenging Leisure Activity Questionnaire is based on the CHAMPS Physical Activity Questionnaire for Older Adults [46] and will serve as a measure of the protective factors social, physical, and cognitive activities. Participants will indicate for each of 44 socially, physically, and cognitively challenging activities whether they performed them at least once during the past 4 weeks. A short 14-item Mediterranean diet questionnaire [47] will assess components of a Mediterranean diet. The measurement of risk and protective factors will serve as the basis for individual feedback in the cognitive health counseling and for the assessment of behavior changes between pretest and posttest assessments.

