### Interventions

Participants will be randomly assigned to one of two groups, the jigsaw puzzle group or the cognitive health counseling group (see Fig. 2). The jigsaw puzzle group will receive the 30-day jigsaw puzzle intervention and the cognitive health counseling, while the cognitive health counseling group will receive the cognitive health counseling only. We will ask the participants of the cognitive health counseling group not to solve any jigsaw puzzles within the 5-week intervention period. Participants of the cognitive health counseling group will receive a jigsaw puzzle after completion of the posttest assessments.

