#### Cognitive health counseling

All participants will receive a 15-minute session of cognitive health counseling in an individual face-to-face setting, including a take-home brochure (see Figs. 1 and 2). The counseling will inform about modifiable protective factors and risk factors for cognitive decline and dementia according to current research evidence. It will be based on the guidelines of the German Association for Psychiatry, Psychotherapy, and Psychosomatics on dementia. In particular, the counselors will explain protective effects of physical, cognitive, and social activities, and a Mediterranean diet. The counseling will further inform about the modifiable risk factors obesity, hypertension, diabetes mellitus, high cholesterol and homocysteine levels, smoking, and alcohol misuse.

In addition, the cognitive health counseling will comprise three telephone calls during the 5-week intervention period. In the first call (t_3_; week 1), participants will receive individual feedback based on their responses in the questionnaires on modifiable risk and protective factors at the pretest assessment. Here, we will give information about potential behavior changes and ask the participants whether they are motivated to adapt any of them. In the second and third telephone-based interview, we will ask for changes in behavior with respect to the predictive factors. Taken together, the behavior change techniques of the cognitive health counseling include the shaping of knowledge about cognitively healthy behaviors (t_2_), providing individual feedback on these behaviors (t_3_), and monitoring behaviors by the study staff with participants’ awareness (t_4_ and t_5_, cf. [48]).

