#### Jigsaw puzzle intervention

Participants of the jigsaw puzzle group will solve jigsaw puzzles on 6 days a week for 5 weeks for at least 1 h per day. Every participant will get the same 300 piece jigsaw puzzle at first (*Beautiful Prague* by RSV; piece size: 2.45 × 2.4 cm). The participants will select subsequent puzzles out of a catalogue with 200, 300, 500, 1000, and 1500 piece jigsaw puzzles of the RSV adult puzzle 2016 collection (piece sizes included: 2.8 × 3.0 cm; 2.45 × 2.4 cm; 2.0 × 1.8 cm; 1.9 × 1.7 cm; and 1.8 × 1.7 cm, respectively).

The intervention will take place at participants’ homes. They will protocol their jigsaw puzzle time in a diary immediately after each jigsaw puzzle session. On each jigsaw puzzle day, participants will note the jigsaw puzzle name, the jigsaw puzzle duration, and if necessary additional comments about their experiences. Immediately after each of the three telephone-based cognitive health counseling sessions, participants will report the content of the diary for the monitoring of the protocol adherence and of the jigsaw puzzle performance (time per connected piece). Finally, the telephone-based interview includes questions about participants’ jigsaw puzzle experience for each solved jigsaw. Jigsaw puzzle experience will include the desire to solve the jigsaw puzzle, the pleasure in solving the jigsaw puzzle, the experienced competence of solving the jigsaw puzzle, and the perceived difficulty of the jigsaw puzzle. We will evaluate all four measures with a single question and a 5-point rating scale that ranges from “very high” to “not at all”. Participants will be able to freely choose their preferred jigsaw puzzles. However, we will recommend them to constantly increase the difficulty and challenge of the jigsaw puzzles through the increase of pieces per puzzle - which is accompanied with a decrease in piece size - as long as this does not reduce their pleasure and fun. These recommendations will depend on the reported perceived difficulty, challenge, pleasure, and fun, and their jigsaw puzzle performance (time per connected piece). If participants report adverse conditions associated with solving jigsaw puzzles (e.g., muscle pain during jigsaw puzzling or the development of a strong craving to solve jigsaw puzzles), the study staff will recommend to reduce puzzle time, not to stick to the protocol of at least 1 h per day, or to stop solving jigsaw puzzles as appropriate.

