### Statistical analysis

The primary efficacy analysis will be based on mixed-effects models' group × time interaction [53] in an intention-to-treat approach [54] that includes all randomly assigned participants with follow-up observations. Effect sizes will include standardized differences in the pretest-posttest change scores between both groups. Standardization will be based on (1) baseline scores and (2) pretest-posttest change scores. In additional analyses, we will account for potential confounding variables such as baseline performance, the number of challenging social, physical, and cognitive activities performed in the past 4 weeks, the pretest-posttest change in these activities, Mediterranean diet in the past 4 weeks, and pre-posttest change in diet, age, education, participants’ test motivation at the posttest assessment, and their expectations of cognitive benefits.

As the primary intention-to-treat analysis is a conservative method, which may underestimate the true effect size of solving jigsaw puzzles for individuals who follow the protocol, we will use a supportive per-protocol analysis, which includes only participants who completed at least 80% of the jigsaw puzzle protocol (≥24 jigsaw puzzle days with a minimum of 45 min). With this supportive analysis, we do not only assess the robustness of effects, but may also receive a more accurate estimate of the true effect size given optimal conditions.

For subgroup and moderator analyses, pre-specified variables comprise baseline global visuospatial cognition, amount of lifetime puzzle experience, number of challenging social, physical, and cognitive activities within the intervention period, age, MMSE, and experienced pleasure in solving jigsaw puzzles.

Finally, we will assess cognitive demands of solving jigsaw puzzles and the transfer potential of gains in jigsaw puzzle skill on gains in the study outcomes by calculating the correlation between jigsaw puzzle skill in the 40-piece puzzle and the study outcomes at baseline.

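### Two of the six pre-specified moderators are measured after randomisation: puzzle pleasure is recorded only in the jigsaw arm, and the intervention-period activity count can be affected by allocation

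*Protocol article*

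**What the plan says.** The Statistical analysis section lists the variables pre-specified for subgroup and moderator analyses. The first two are baseline global visuospatial cognition and lifetime puzzle experience. The others are "number of challenging social, physical, and cognitive activities within the intervention period, age, MMSE, and experienced pleasure in solving jigsaw puzzles". That makes six.

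On pleasure, the Jigsaw puzzle intervention section says that "the telephone-based interview includes questions about participants’ jigsaw puzzle experience for each solved jigsaw". It then defines the construct: "Jigsaw puzzle experience will include the desire to solve the jigsaw puzzle, the pleasure in solving the jigsaw puzzle", together with competence and perceived difficulty. The Procedure section places these ratings in one arm: "These telephone-based interviews will also serve to monitor the jigsaw puzzle experience and protocol adherence in the jigsaw puzzle group". For the other arm, the Interventions section says: "We will ask the participants of the cognitive health counseling group not to solve any jigsaw puzzles within the 5-week intervention period".

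On activities, the section on predictive variables describes a questionnaire that asks, for each of 44 activities, "whether they performed them at least once during the past 4 weeks". It serves to measure change between pretest and posttest, so a pretest value exists in both arms. Counseling, which both arms receive, targets these activities: "the counselors will explain protective effects of physical, cognitive, and social activities, and a Mediterranean diet". The Discussion allows that counseling might change behaviour differently in the two groups. It plans to compare the groups on that change and to account for it in additional analyses.

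**The concern.** A moderator analysis asks whether the effect of allocation differs between kinds of participant. Each such comparison keeps the protection of randomisation only if the moderator is fixed before allocation and observed in both arms. Four of the six variables meet this: baseline cognition, lifetime puzzle experience, age and MMSE. Two do not.

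Pleasure describes an experience that only one arm is given. The activity count covers a period in which the two arms are already living differently, one of them committed to at least 30 hours of puzzling (30 days × 1 h).

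At stake is how the results may be read. A pre-specified moderator is normally taken as evidence on who benefits. For pleasure, the data cannot answer that question. For activities, the answer may mix the effect of allocation on activity with the effect of activity on outcome.

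**Working it through.** **1. The plan's own figure.** The Power analysis section gives 50 per group, 15% dropout, f = 0.1, r = .85, α = 0.05 and power 90%. With N = 100 × 0.85 = 85 and m = 2 measurements, the noncentrality is λ = f² × N × m / (1 − r) = 0.01 × 85 × 2 / 0.15 = 11.33. The noncentral F with 1 and 83 degrees of freedom gives power 0.914 (0.911 at N = 84, 0.917 at N = 86). The stated 90% is reproduced. It concerns the primary group × time term; the article gives no figure for the moderator analyses.

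**2. Pleasure: which values exist.** Ratings are attached to solved puzzles and collected in calls that monitor the jigsaw group. The section on blinding confirms the asymmetry: it exempts the questions on puzzle experience and adherence from the equal staff contact. The baseline puzzle-history items cover degree, hours and pieces, not pleasure. Both arms do the 40-piece test puzzle, but no pleasure rating is described for it. Control values are therefore 0 of 50.

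**3. Pleasure: what can be estimated.** With two time points, group × time × pleasure equals group × pleasure in a model for change, with columns 1, g, P and gP (g = 1 for jigsaw).
- If controls are given any constant c, then P − gP = c(1 − g), a combination of the first two columns. The rank is 3 of 4.
- If controls are left missing, g = 1 throughout, so g repeats the intercept and gP repeats P. The rank is 2 of 4.

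In both cases the interaction has no unique estimate. What remains is the slope of change on pleasure within the jigsaw arm, in about 50 × 0.85 = 42.5 people. That slope is observational. Under the Jigsaw puzzle intervention section, advice on difficulty depends on reported pleasure and puzzle performance, so pleasure is tied to which puzzles are tackled.

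**4. Activities: an illustration with assumed inputs.** Let U be a trait that correlates 0.3 with change. The SD of change is √(2 × (1 − 0.85)) = 0.548, so the slope of change on U is 0.3 × 0.548 = 0.164. The true group effect on change is set at a constant 0.40, with no moderation, and 42 per arm. The measured activity count is A = U in controls.
- If A = U + a in the jigsaw arm, then U = A − a, and the group term at a given A is 0.40 − 0.164a. For a = −0.5 this is 0.48; for a = +0.5 it is 0.32. The interaction stays at zero.
- If A = 0.5U − 0.5 in the jigsaw arm, then U = 2A + 1. The group term at A = 0 is 0.40 + 0.164 = 0.56, and the interaction is 2 × 0.164 − 0.164 = 0.16, although none exists.

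Simulation with 4,000 runs per scenario agrees:

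| Effect of allocation on activities | Group term | Interaction | Interaction test rejects |
|---|---|---|---|
| none | 0.40 | 0.00 | 5.3% |
| −0.5 SD | 0.49 | 0.00 | 4.6% |
| +0.5 SD | 0.32 | 0.00 | 4.5% |
| −0.5 SD, spread halved | 0.56 | 0.16 | 13.6% |

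A mean shift alone biases the group effect conditional on activity but does not create a false interaction. In these scenarios a false interaction appeared only when allocation also changed the spread.

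**The case against.** The article lists variables and writes no model. It speaks of subgroup and moderator analyses together, so pleasure could be meant as a split or predictor within the jigsaw arm, which can be run. A reader might infer that the pleasure analysis is impossible altogether. The documents do not support that: only moderation of the between-group effect is out of reach. What stands is that the article puts pleasure in the same list as age and MMSE and does not say that it is a within-arm analysis.

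A reader might also infer that activities are affected by allocation. The Discussion says only that a differential effect cannot be excluded, and both arms get the same counseling, so its promotion of activities does not by itself produce a difference. The authors also plan to compare the arms on activity change. That diagnostic is useful, but it does not turn a post-randomisation count into a baseline moderator. Nor does the illustration show that the activity interaction is simply invalid: in two of the three scenarios with an effect of allocation, the false-positive rate stayed near 5%.

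Finally, concurrent activity is a question in its own right, which the pretest count does not answer. This stands, and is a reason to allow the later count as an exploratory analysis.

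**Conclusion.** The point holds in a limited form. Two of six pre-specified variables are post-randomisation. For pleasure the conclusion rests on the text and on algebra: with no control values, it cannot moderate the between-group effect, and any result is a within-arm association. For activities the conclusion is a risk, not a demonstrated bias. Subgroups may not be comparable between arms, and the conditional group effect may be biased if allocation shifts activity. The sizes shown (0.32 to 0.56 against a true 0.40, and up to 13.6% false interactions) depend on the assumed 0.3 correlation and the assumed shifts.

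The consequences are confined to secondary analyses. The primary group × time analysis, the sample size and the stated power are untouched, and the other four moderators are sound. The correction should be made, but nothing about the trial's main result depends on it.

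**What to change.** - Take experienced pleasure off the moderator list. Report it as an exploratory association with change within the jigsaw arm, adjusted for baseline performance, and state that randomisation does not protect it.
- Name the pretest activity count as the pre-specified activity moderator.
- If the intervention-period count is kept, label it exploratory and post-randomisation, and present it beside the planned comparison of activity change between arms.
- Leave baseline cognition, lifetime puzzle experience, age and MMSE as they are.

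The cost is a sentence or two in the analysis plan. All the data are already to be collected, and no sample size changes. The one small loss is that the pretest count speaks to prior lifestyle, not to activity alongside the puzzles.

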### Measures

All outcomes of the study are continuously scaled and we will assess the mean change between baseline (t_1_) and posttest assessments (t_6,_ approximately 5 weeks after t_1_). The outcome domains and their specific measurement, and the assessment of participants’ expectations, predictive variables of cognitive decline, and adverse events are described in the following sections.

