The study assesses secondary visuospatial daily functioning outcomes both objectively and subjectively. The objective assessment of daily life functioning comprises three visuospatial subtests of the Timed Instrumental Activities of Daily Living (TIADL) [38, 39] (sub-scores: seconds for correct completion of task A - finding a telephone number*,* task B - making change*,* and task C - reading the list of ingredients on cans; objective daily functioning score: average of all three *z*-standardized sub-scores). Eleven visuospatial items of the Cognitive Failures Questionnaire will assess subjective function in everyday life (subjective daily functioning score: sum of points) [40, 41].

Self-report questionnaires will serve to assess secondary psychological outcomes. We will measure psychological well-being during the past 2 weeks with the World Health Organization (WHO)-5 Well-Being Index [42], general self-efficacy with the Generalized Self-Efficacy Scale [43], and perceived stress during the past month with the Perceived Stress Scale-14 [44].

We will use a 40-piece jigsaw puzzle (image: Rothenburg ob der Tauber by Ravensburger Spieleverlag GmbH (RSV); piece size: ca. 2.45 × 2.4 cm) to measure jigsaw puzzle skill. Thereby participants will complete the frame first and then the inner section of the puzzle (sub-scores for frame and inner section: seconds per connected piece; max. time for each task: 300 s; jigsaw puzzle score: average of both sub-scores).

In case of floor or ceiling effects (skewness ≥ 1 or ≤ − 1), we will use skewness minimization transformations (Blom transformations [45]) for all relevant ability scores and sub-scores. To increase measurement reliability and therefore the power of the study, the same psychologist will conduct pretest and posttest assessment of each participant, if possible. In addition, we will apply different methods to detect data entry errors, including range checks, plotting of pretest and posttest scores, and assessment of the retest-reliability for each score. Low retest-reliability of the primary outcome (*r* < .80) will result in double data entry.

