#### Power analysis

The probability to find a significant effect with 50 included participants per group, a dropout rate of 15%, a small true effect size of *f* = 0.1, pretest-posttest correlation of *r* = .85, and an α-error of 0.05 is 90%. We used G*Power 3.1.6. for power analysis [55].

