Blinding of participants is by nature not feasible in behavioral intervention studies as participants are always aware of what they are doing. Thus, expectation effects can never be fully excluded. Multiple approaches to minimize expectation effects will be used and participants’ expectations with regard to performance improvement will be measured in a telephone-based interview approximately 9 days prior to the posttest assessment. Thus, it will be possible to statistically account for potential expectation effects.

Even if not expected, the selected outcomes of the study may not cover the cognitive abilities that are actually engaged and improved through jigsaw puzzling (e.g., verbal working memory) or may include abilities that are not recruited and improved through the intervention (e.g., cognitive flexibility). To prevent this problem, the selection of the outcomes was based on a cognitive task analysis of jigsaw puzzling that indicated the expected cognitive demands [58, 59]. Furthermore, we will assess the association between the outcome measures and jigsaw puzzle skill at baseline, in order to validate the recruited cognitive abilities of jigsaw puzzling [60] and the transfer potential of gains in jigsaw puzzle performance on gains in the respective outcomes [61]. Finally, there is a not fully preventable risk that gains in outcomes may be a result of skill acquisition or newly learned strategies rather than the improvement of broad cognitive abilities [14]. However, in contrast to many previous cognitive training studies, we use a large set of transfer tasks and these task paradigms are substantially dissimilar from the training task. Thus, we avoid the risk that skill-induced or strategy-induced gains in single and structurally similar tasks with the training task will be misinterpreted as gains in broad cognitive abilities.

Finally, we cannot fully exclude that the cognitive health counseling intervention that is conducted in both groups may have a differential effect between the groups. However, we will assess this potential by evaluating group differences in behavioral changes in cognitive, physical, and social activities, and in Mediterranean diet. In additional analyses of the group effect on the study outcomes, we will statistically account for these behavioral changes (see “Statistical analysis”).

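### The baseline correlation of puzzle skill with the outcomes can show shared cognitive demands but cannot estimate or test the stated relation between gains

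*Protocol article*

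**What the plan says.** The last paragraph of Statistical analysis (before Power analysis) names two targets: the cognitive demands of puzzling, and "the transfer potential of gains in jigsaw puzzle skill on gains in the study outcomes". One method is given for both, namely "calculating the correlation between jigsaw puzzle skill in the 40-piece puzzle and the study outcomes at baseline".

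The Discussion repeats the pairing. The method there is "we will assess the association between the outcome measures and jigsaw puzzle skill at baseline", and its purposes are to validate which abilities puzzling recruits and to assess "the transfer potential of gains in jigsaw puzzle performance on gains in the respective outcomes".

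Three other places bear on which data will exist:

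- Secondary outcomes introduces the skill measure: "We will use a 40-piece jigsaw puzzle".
- Procedure says of the posttest visit: "we will assess the same outcomes as in the pretest assessments in the 1.5-h posttest assessment".
- Measures states: "All outcomes of the study are continuously scaled and we will assess the mean change between baseline" and posttest.

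Nowhere does the article plan an analysis that relates change in puzzle skill to change in an outcome.

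**The concern.** The second target relates one change to another. The planned statistic contains no change, because it describes how people differ from one another before anyone has been trained. Such a correlation can arise from anything the two measures share, for example general ability or age, whether or not improving one would improve the other. A low baseline correlation likewise does not rule out related gains.

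The Discussion offers this analysis, together with a cognitive task analysis, in answer to the worry that the chosen outcomes may not match the abilities that puzzling engages and improves. The part about abilities engaged is well served. A sentence in the trial report about gains in skill carrying over to gains in outcomes would have no support from this statistic. The article fixes the method explicitly, so this is not a detail left to a fuller document.

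**Working it through.** **The plan's own figure.** The correlation analysis has no stated figure. The only one nearby is the 90% power of the primary group × time test. It is reproduced here because its inputs are reused.

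- Inputs (Power analysis): 50 per group, 15% dropout, f = 0.1, pretest-posttest r = .85, α = 0.05.
- Completers: 100 × 0.85 = 85 in all, or 50 × 0.85 = 42.5 per group.
- Noncentrality with m = 2 occasions: λ = f² × N × m / (1 − r) = 0.01 × 85 × 2 / 0.15 = 11.33, with 1 and 83 degrees of freedom.
- Power: 91.4%, within two points of the stated 90%. The present point does not depend on it.

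**Does the baseline correlation determine the gain-gain correlation?** Score both measures so that higher is better, with unit variance at each occasion. Let

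- r = pretest-posttest correlation, .85 for both measures (the article gives it for the power calculation only; its use for puzzle skill is an assumption);
- c = puzzle-outcome correlation, assumed equal at pretest and posttest;
- q = correlation of one measure at pretest with the other at posttest, assumed the same in both directions.

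Then:

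- Covariance of the two gains = c − q − q + c = 2(c − q).
- Variance of each gain = 2(1 − r) = 0.30.
- Gain-gain correlation = 2(c − q) / [2(1 − r)] = (c − q) / 0.15.

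The planned analysis estimates c. It gives no information on q.

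| c (assumed) | q (assumed) | Gain-gain correlation |
|---|---|---|
| .50 | .50 | 0 / 0.15 = .00 |
| .50 | .41 | .09 / 0.15 = +.60 |
| .50 | .56 | −.06 / 0.15 = −.40 |
| 0 | −.09 | .09 / 0.15 = +.60 |

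Simulation with 400,000 draws per row gave .00, .60, −.40 and .60.

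**Are these values of q admissible?** The 4 × 4 correlation matrix must have no negative eigenvalue. Two of its eigenvalues are 1 + c − r − q and 1 − c − r + q. These require q to lie between c − 0.15 and c + 0.15. For each c tried (0, .3, .5, .6) this was the binding limit. The gain-gain correlation could therefore lie anywhere from −1 to +1, whatever the baseline correlation.

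**Could the planned data address gains?** By Fisher's z, the correlation detectable with 80% power at two-sided 0.05 is tanh[(1.960 + 0.842) / √(n − 3)]:

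- n = 42 (puzzle group): tanh(2.802 / √39) = .42.
- n = 85 (all completers): tanh(2.802 / √82) = .30.

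An observed r of .30 with n = 42 would have a 95% CI of about .00 to .55.

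**Is puzzle skill measured at posttest?** The 40-piece puzzle is described under Secondary outcomes, Procedure repeats the same outcomes at posttest, and Measures assesses change in all outcomes. Posttest administration follows by inference. The schedule figure, which would settle it, is not shown.

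**The case against.** The strongest reply is that the article says transfer potential, not transfer. Outcomes that share abilities with puzzling are those that could plausibly benefit, and baseline overlap is relevant evidence for that. The Discussion also cites a separate source for this use, which cannot be examined here. Much of this stands: the baseline correlation is informative about plausibility, and it would be too strong to say that it has no bearing on gains. But the wording in both places is potential of gains on gains. Plausibility drawn from a shared ability neither estimates nor tests that.

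A reader might also infer that the trial's protection against misreading skill gains as broad cognitive gains rests on this correlation. It does not. The Discussion bases that protection on a large set of transfer tasks unlike the training task. Nor is the efficacy claim at risk: whether the intervention changes the outcomes is tested by the randomised group × time comparison.

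Finally, a change-on-change analysis does not identify transfer either. Randomisation gives no protection within one arm, and retest practice, test motivation and same-day state can make two gains correlate without any transfer. This stands in full. It is why such an analysis should be optional and exploratory, and why rewording alone would be a sufficient remedy.

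**Conclusion.** The point holds in limited form. One statistic is assigned to two questions, and it answers only the one about cognitive demands. For the question about gains it leaves the quantity undetermined: at r = .85, an assumed baseline correlation of .5 fits gain-gain correlations of −.40, 0 or +.60.

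Those figures illustrate the range and do not predict the size of any error in this trial. They rest on r = .85 holding for both measures and on equal puzzle-outcome correlations at the two occasions. The general conclusion, that data from one occasion cannot estimate a relation between changes, needs neither assumption.

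The analysis is supplementary, with no stated hypothesis test or success criterion and no role in the sample size. The point is minor.

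**What to change.** 1. In Statistical analysis and in the Discussion, limit the baseline correlation to the cognitive-demands aim, and reword both so that no statement about gains relies on it. This costs a few words and is sufficient on its own.
2. If a relation between gains is to be assessed, add an exploratory regression of change in each outcome on change in the 40-piece puzzle score. Fit it within the puzzle group, or in all completers adjusted for group, with the baseline values of both measures as covariates. Report estimates with 95% CIs.
3. State the limits of that analysis alongside it: low precision (the detectable correlations shown above) and an observational comparison open to practice, motivation and same-day effects.
4. Confirm that the 40-piece puzzle is given at posttest. If it is, step 2 needs no new data collection.
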